### Interventions

The trial will be 10 weeks long, during which time patients will undergo two sets of phototherapy, exercise, or placebo procedures per week. Phototherapy will be applied 30 min before each exercise bout, and treatment sessions will be carried out Tuesdays and Thursdays each week. For eligible patients, the research will record outcome parameters at baseline prior randomization and 48 h after the last day of intervention. This evaluator will be blinded to the allocation of the patients into the respective groups.

### Assessment and result reliability

Two therapists will guide the interventions at each basic health center. To ensure the feasibility of the study and the reliability of the results, all therapists and researchers will be trained in data collection procedures before the start of the trial. Moreover, the results will be analyzed by an independent investigator without knowledge of the allocation of patients to their experimental groups.

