## Methods/Design

### Study design

The EXTRAPHOTO trial (ClinicalTrials.gov identifier NCT02279225) is a multicenter randomized controlled clinical trial comparing the use of exercise training, phototherapy, and exercise training plus phototherapy for pain control in women with two comorbidities (FM and TMD). As part of a simultaneous recruitment process, in the EXTRAPHOTO trial we will identify participants with target disorders in a database of the Unified Health System of Sao Paulo, Brazil. A preliminary analysis showed that patients at three centers with FM specialties are eligible: (1) the Rheumatology Clinic of Nove de Julho University, Sao Paulo, Brazil; (2) the basic health center of Sao Paulo, Brazil; and (3) the basic health center of Sao Paulo in Sao Bernardo do Campo, Brazil. The study procedure will follow the guidelines of the Consolidated Standards of Reporting Trials statement. All participants will receive data on the study aims and experimental procedures. We will obtain signed, written informed consent forms from each patient before inclusion in the study. The trial scheme is detailed in Fig. 1.

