### Population and sample size

In a literature review, we found that FM prevalence is higher in women between ages 35 and 60 years than in men [21]. All women patients aged ≥ 35 years and referred for FM and TMD diagnostic evaluation were eligible for inclusion in the present trial. Patient eligibility comprises an evaluation of medical history, physical examination, and dental and rheumatologic routine evaluations. Moreover, patients had to have undergone FM screening as reported by the American College of Rheumatology using the Fibromyalgia Impact Questionnaire (FIQ) 1. The TMD diagnosis had to be reported on the basis of TMD research diagnostic criteria (axes I and II) [22]. The sample size calculation was based on a previous study by Consalter et al. [23] in which the TMD prevalence was 80 % in patients with FM. A 95 % reliability and a 10 % error rate was assumed to estimate the sample size (n) as follows [24]:$$ n={\left(\frac{z_{a/2}\sqrt{p\left(1-p\right)}}{\varepsilon}\right)}^2={\left(\frac{1.96\ast \sqrt{0.8\ast 0.2}}{0.1}\right)}^2 $$

A total of 60 women will be randomized for this trial, with 20 women allocated per group.

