### Statistical analysis

Pain will be the primary endpoint and will be determined using a VAS, an algometer, the FIQ, and the McPQ. Quality of life as assessed by SF-36, salivary serotonin level, and overall parameters of pain will be secondary endpoints. Statistical analysis will be performed using IBM SPSS software (version 13.0; IBM, Armonk, NY, USA), and a two-sided *P* value <0.05 will be considered significant. The intragroup and intergroup comparisons will be carried out with two-way repeated-measures analysis of variance with post hoc Bonferroni correction or the Kruskal-Wallis test with a post hoc Dunn test. The choice of tests will be based on the distribution (normal or non-normal) of the data by the Shapiro–Wilk test. For categorical data, χ^2^ statistics will be used.

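### The stated group-by-time pain analysis of a three-centre, therapist-delivered trial has no centre term: a small matter of precision and chance imbalance, not of bias

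*Protocol article*

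**What the plan says.** All references are to the protocol article.

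- **Study design**: the study "is a multicenter randomized controlled clinical trial", and "patients at three centers with FM specialties are eligible". The three are a university rheumatology clinic and two basic health centres.
- **Assessment and result reliability**: "Two therapists will guide the interventions at each basic health center". The training mentioned there is in data collection; training in delivering the interventions is not mentioned.
- **Randomization, blinding, and experimental groups**: individual women are randomised to four groups, and one university programme runs enrolment and randomisation. No randomisation method, blocking or stratification factor is named. One further researcher guides the exercise training, and a separate blinded investigator assesses outcomes.
- **Statistical analysis**: "The intragroup and intergroup comparisons will be carried out with two-way repeated-measures analysis of variance with post hoc Bonferroni correction", or Kruskal-Wallis with Dunn's test, chosen by the Shapiro-Wilk result. A two-sided P "value <0.05 will be considered significant". Centre and therapist do not appear.
- **Population and sample size**: "A total of 60 women will be randomized for this trial, with 20 women allocated per group".

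**The concern.** Part of the delivery depends on who guides it: for example, stretching is taken to mild discomfort and treadmill work is steered to a heart-rate target. If site staff differ, the mean improvement in pain may differ between centres. The therapists act between baseline and follow-up, so such a difference falls on change, which is what the group-by-time contrast measures.

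Two things follow if the model leaves centre out. In a small four-arm trial the arms may by chance draw unequally from the centres, and nothing adjusts for it. Variation between centres in change also stays in the residual, which costs power, or makes the test conservative if centre was balanced by stratification. The analysis method is stated here, so this part does not rest on the article's silence.

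**Working it through.** **Inputs.** The plan gives no figure on centre effects. Arm size comes from the total: 60/4 = 15. The article also says 20 per group, and 4 × 20 = 80, so the two disagree; I use 15 and mention 80 where it matters. The article's sample-size formula gives (1.96 × 0.4/0.1)² = 61.5, close to the stated 60, but it concerns a prevalence and says nothing about centre. Assumed, because the documents give no values: three centres of 20 women, a centre share of the variance of change (ICC) of 0 to 0.20, and one arm differing from the others by 1 SD of change.

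**Step 1: what the stated test responds to.** With two occasions, the group-by-time F test is the one-way analysis of variance of change. A centre difference in pain level that is the same at both visits cancels; only centre differences in change matter. For the same reason, a centre main effect alone would leave the group-by-time test unchanged. Centre-by-time is the term that acts on it.

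**Step 2: error rate and power.** I simulated change scores (10,000 trials per setting, 60 women, F test at 5%). Unstratified means 15 per arm permuted over all women; stratified means 5 per arm in each centre. Entries are without / with a centre term, in per cent.

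| ICC | Type I, unstratified | Type I, stratified | Power, unstratified | Power, stratified |
|---|---|---|---|---|
| 0 | 4.7 / 4.7 | 4.9 / 4.9 | 78.3 / 77.0 | 78.4 / 78.3 |
| 0.05 | 4.4 / 4.7 | 4.5 / 4.9 | 79.2 / 79.2 | 79.0 / 80.6 |
| 0.10 | 4.4 / 4.7 | 3.9 / 4.9 | 80.2 / 81.8 | 79.6 / 83.0 |
| 0.20 | 4.4 / 4.7 | 3.1 / 4.9 | 81.9 / 86.1 | 81.2 / 87.4 |

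The Monte Carlo standard error is about 0.2 points for the error rates and 0.4 for power. Power should be compared within a row, since total variance is held at 1.

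A second set of runs (6,000 per setting, slightly unequal centres) gave:
- unstratified type I error without the term: 4.9 to 5.1%;
- stratified type I error without the term: 4.3% at ICC 0.10 and 3.4% at 0.20;
- unstratified power without and with the term: 78.9 and 77.3% at ICC 0, and 81.5 and 85.9% at 0.20;
- with 80 women, unstratified, at ICC 0.20: 92.4 and 95.5%.

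**Step 3: chance imbalance without stratification.** 20,000 permutations of 60 women into 4 × 15, with 20 per centre:
- some pair of arms differs by at least 5 women from some centre: 58%;
- one named pair, any centre: 19% (14% with centres of 36/12/12);
- one named pair and one named centre: 8.2% (exact hypergeometric calculation).

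The 58% is a maximum over 6 arm pairs × 3 centres = 18 gaps, so the lower figures describe any contrast fixed in advance. For scale, if two centres differed by an assumed 1 cm in mean VAS change and the arms exchanged 5 of 15 women between them, the contrast would move by 5/15 × 1 = 0.33 cm.

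**The case against.** A reader might infer that operator and site differences pass straight into the four-arm comparison. The documents do not support that. Randomisation is of individuals through one programme, so arm is not tied to centre. Chance imbalance is part of the sampling error that the F test already reflects, as the type I rates show. Excess error appears only if arm is tied to centre: in the second set of runs, 18, 32 and 54% at ICC 0.05, 0.10 and 0.20. Nothing in the article describes such an allocation.

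It is also tempting to say that allocation ignores centre. The article names no randomisation method at all, and a condensed article commonly leaves stratification factors to the full protocol, so its silence cannot be read as unstratified allocation. The same defence is weaker for the analysis, because specific tests are named and Kruskal-Wallis as named cannot carry a centre term.

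Three further limits stand. That different therapists work at each centre is a fair inference, not a stated fact, and the sentence on therapists does not cover the university clinic. The blinded assessor, who is separate from the therapists, limits site differences in measurement, though not in delivery. No centre difference in outcome is given anywhere.

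**Conclusion.** The point holds as a minor one. The stated analysis leaves centre out of a multicentre trial with site-based delivery. The consequence is some uncorrected chance imbalance and a small loss of precision, or a conservative test if allocation is stratified by centre; it is not systematic bias or a raised false-positive rate.

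The size depends on an ICC that the documents do not give. With 15 per arm, adding the term ranges from a loss of 1 to 2 points of power (no centre differences, unstratified) to a gain of roughly 4 to 7 points (ICC 0.20, the upper end applying under stratification). Near ICC 0.05 without stratification it makes no difference. The case for the term is stronger if allocation is stratified, because it then restores the nominal 5% and costs almost nothing.

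Separately, one section gives exercise guidance to a single researcher and another gives the interventions to two therapists at each basic health centre. These passages must be reconciled, since the answer decides whether the operator varies by site.

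**What to change.** - In the pain model, include centre and centre-by-time. Equivalently, analyse change, or follow-up adjusted for baseline, with centre as a fixed factor.
- Where Kruskal-Wallis would have been used, name a rank test stratified by centre.
- State whether allocation is stratified by centre. If it is not, use permuted blocks of varying size within centre for women not yet randomised; allocation is already under way according to the trial status section.
- Record centre and treating therapist, and tabulate the arms by centre.
- Reconcile the two accounts of who guides the exercise.

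Cost: 2 degrees of freedom (error 56 to 54 for the analysis of change with 60 women), with the power loss given above if centres do not differ and allocation is unstratified. Stratified lists need one list per centre, and block sizes must be kept from the therapists.

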### Phototherapy

Phototherapy will be carried out with a PainAway™ nine-diode cluster portable device (Multi Radiance Medical, Solon, OH, USA). This portable device was specifically designed for pain relief and has two operating modes: mild and severe. Because of the characteristics of pain that patients with FM, we decided to use the device at the mild setting. The device has two identical application hand pieces—one active tip and the other for placebo procedure without energy, both equipped with a similar sound device. These equipment pieces are required to blinding applicator research and patients. Thus, the researcher who will apply phototherapy and the patient will not know which tip was used (active or placebo). The irradiation will be applied only in the tender points in which pain has been reported by the participants. These tender points can be occipital, cervical (near the C7), trapezius, supraspinatus, second costochondral joint, lateral epicondyle and gluteal/sacrum, and greater trochanter on the medial knee border. The temporomandibular joint (bilaterally) will be another irradiation target because of TMD. Each point will be irradiated for 300 s, in which 39.3 J of total energy will be delivered for each irradiation point. An independent researcher will be responsible for controlling the on or off phototherapy device because therapists and patients will be blinded to the procedure. The applicator researcher and patient will be wearing eye protection devices. The CON group will be subjected to the same procedures as the groups subjected to the PHO intervention. The phototherapy device to be used is shown in Fig. 2. All parameters of the phototherapy device are shown in the Table 1.

**Fig. 2 Fig2:**
[figure not shown]
Phototherapy device that will be used to treat pain

**Table 1 Tab1:** Phototherapy parameters

Parameters	Pulse
	1 Superpulsed infrared
Wavelength of lasers (nm)	905
Frequency (Hz)	1000
Average optical output (mW)	0.9
Power density (mW/cm^2^)	2.25
Peak power (W)	8.5
Dose (J)	0.3
Energy density (J/cm^2^)	0.75
Spot size of laser (cm^2^)	0.4
Number of LEDs	4 Red
Wavelength of LEDs (nm)	640 (±10)
Frequency (Hz)	2
Average optical output (mW), each	15
Power density (mW/cm^2^), each	16.66
Dose (J), each	4.5
Energy density (J/cm^2^), each	5
Spot size of LED (cm^2^), each	0.9
Number of LEDs	4 Infrared
Wavelength of LEDs (nm)	875 (±10)
Frequency (Hz)	16
Average optical output (mW), each	17.5
Power density (mW/cm^2^), each	19.44
Dose (J), each	5.25
Energy density (J/cm^2^), each	5.83
Spot size of LED (cm^2^), each	0.9
Magnetic field (mT)	35
Treatment time (s)	300
Aperture of device (cm^2^)	4
Total energy delivered (J)	39.3

*LED* light-emitting diode

### Exercise training protocol

The EXT protocol will be carried out according to the guidelines of the American College of Sports Medicine [26], and a previously published protocol will be applied for the treatment of tender points of the patients with FM [25]. The protocol consists of stretching and aerobic exercise two times per week for 10 weeks. Active static stretching will be applied to the following muscle groups: biceps, trapezius, latissimus dorsi, pectoralis, paraspinal, hamstrings, and quadriceps. Each stretching exercise will be performed three times for 30 s, and 30 s of rest will be allowed between each stretch. The stretch will be conducted to produce mild discomfort. The aerobic exercise will be carried out on an electronic motorized drive (LX-150; Movement, Sao Paulo, Brazil) without inclination for 30 min per session. The exercise will be guided at an intensity of 75 % of age-predicted maximum heart rate (220 − age in years).

Exercises for TMD will be carried out as reported in detail elsewhere [27]. Exercises will be performed with the patient in a sitting position and repeated three times for every movement. A maximum oral opening will be required for the first exercise; the second exercise will be a tongue slippage on the palate; and the third exercise will be oral lateralization to the right and left with contraction of the masseter muscle. This exercise will be conducted with the participant’s mouth filled with air for 3 s. Ultimately, circular fingertip motions will be applied with slight pressure on the temporomandibular joint and masseter muscle [27, 28].

### Outcome parameters

The outcome parameters described below will be evaluated at baseline and 24 h after the last day of the experimental protocol.

#### Personal and anthropometric data

We will collect data on participants’ occupation, education level, marital status, social security number, home address, age, body weight, and height.

#### Overall parameters of pain

To assess overall parameters of pain, we will gather information on daily duration of pain, pain tender points, number of days with a high pain level, sleep quality, main features that show accentuation or worsening of pain, incidence of stiffness and pain, jaw locking, and morning fatigue.

#### Visual analogue scale

We will use a visual analogue scale (VAS) to assess pain level. The VAS consists of a limited strip of 10 cm in length. This strip has at its ends the anchor terms *no pain* and *worst pain possible*. The patient will be instructed to report the level of pain sensation to a point along this line, with the scores ranging from 0 to 10 and obtained by measuring the distance between the end anchored by the term *without pain* and the point marked by the participant [29]. Additional analysis will include changes from randomization to the end of withdrawal (week 10) in an adapted Portuguese version of the McGill Pain Questionnaire (McPQ) [30].

#### Algometry

A digital algometer (DD-200; Instrutherm, Sao Paulo, Brazil) will be used to evaluate pain sensibility through the application of pressure. The algometer will be positioned to read specific FM tender points and TMD joints using the rubber tip measuring 1 cm^2^ in direct contact with the skin. A gradually increasing pressure will be applied to all points until the patient reports feeling pain, at which point the researcher will stop applying pressure and display values will be recorded. The procedures will be performed only once to each point, and a 30-s rest period will be given between readings [29].

#### Fibromyalgia symptoms and quality of life

Outcome parameters will be evaluated with the FIQ. The FIQ is a multidimensional instrument developed to assess several FM symptoms (pain, fatigue, stiffness, tenderness, sleep disorders, depressed mood, anxiousness, problems with memory, imbalance, sensitivity to non-painful stimuli, and performing daily tasks) [29]. The Medical Outcomes Study 36-item Short Form Health Survey (SF-36) will also be used [29].

#### Salivary serotonin

Concentration of serotonin in the saliva is relevant to nociception and the pathogenesis of chronic pain syndromes seen in FM [31]. Thus, mean serotonin changes from randomization to the end of withdrawal will be evaluated in 25-μl salivary samples by using a competitive enzyme-linked immunosorbent assay (ELISA) according to the manufacturer’s instructions (Human Serotonin ST ELISA Kit; MyBioSource, San Diego, CA, USA). The samples will be collected with cotton swabs into plastic tubes without any stimulation and frozen (−80 °C). Patients will be instructed to rinse their mouths with water and not to eat or drink 30 min before the samples are collected. The ELISA plates will be read with a SpectraMax Plus 384 spectrophotometer (Molecular Dynamics, Sunnyvale, CA, USA) at a wavelength of 400 nm [31].

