## Abstract

**Background:**

Fibromyalgia (FM) is a syndrome most prevalent in women, in whom it is characterized mainly by chronic pain. An important issue is that many patients with FM are reported to have temporomandibular dysfunction (TMD), and the coexistence of these pathologies generates a clinical outcome of high complexity. The literature is unclear regarding an effective therapy for reducing pain in patients with both comorbidities. Exercise training and phototherapy (low-level laser therapy with light-emitting diode) are two of the approaches used to treat pain. Thus, the aim of this study is to assess the potential role of exercise training plus phototherapy in reducing chronic pain in women with FM and TMD. A further aim is to determine whether the interventions can improve quality of life and modulate endogenous serotonin.

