## Background

Fibromyalgia (FM) is a chronic syndrome characterized mainly by pain, nonrestorative sleep, fatigue, morning stiffness, depression, and cognitive disorders [1, 2]. Patients with FM often show widespread pain in the presence of tender points (expressed as mild or greater tenderness), which provide the most sensitive, specific, and accurate criteria for making the diagnosis [1, 3]. Using this classification, almost all patients with FM are women because they have more tender points than do men [4]. Overall, FM symptoms lead to significant reduction in functional capacity and quality of life [2, 5, 6]. Developing treatment teams is useful, including clinicians with expertise in patient education, exercise training interventions, and cognitive behavioral therapy [7–9]. An optimized treatment can be provided using the following steps: (1) overall recommendation (e.g., patient education), (2) nonpharmacologic (e.g., exercise, cognitive behavioral therapy, alternative medicine, and central nervous system neurostimulatory intervention), and (3) pharmacologic (e.g., tricyclic complexes, gabapentinoids, γ-hydroxybutyrate, naltrexone, cannabinoids, selective serotonin reuptake antagonists, nonsteroidal anti-inflammatory drugs, and opioids) [4].

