### Recruitment and inclusion criteria

The recruitment methods include direct referral of patients who consult for FM, in which TMD also will be investigated. A rheumatologist and a dentist will make the diagnoses of FM and TMD, respectively. A physician at each FM medical center will participate. A compatible diagnosis of FM will be obtained on the basis of evaluation criteria similar to those previously well defined [25]. The recruitment of 60 patients is planned to be finished within 24 months. Inclusion criteria are as follows: women ≥ 35 years of age presenting with at least a 5-year diagnosis of FM and TMD, optimized drug treatment, cognitive independence to respond to inquiries, functionally independent regarding daily physical activity, availability and ability to fully comply with the training process and phototherapy, and no contraindication to the research procedures. All centers will be informed about the EXTRAPHOTO trial and its inclusion criteria during department meetings. Exclusion criteria are patients in a prior regular and structured physical activity program; missing more than three times from treatment; presence of psychiatric disorders, missing teeth, and/or use of dentures; a history of trauma to the face; currently undergoing orthodontic intervention; and any contraindication to exercise or phototherapy. The FM symptoms can be confused with other disorders. Thus, women for whom there are suspicions of any of the following disorders will be excluded: osteoarthritis, bursitis, tendinitis, rheumatoid arthritis, palindromic rheumatism, polymyalgic rheumatic disease, hydroxyapatite crystal diseases, systemic lupus erythematous, dermatomyositis-polymyositis complex, Lyme disease, hypothyroidism or hyperthyroidism, hyperparathyroidism, previous history of hepatitis, and history for Epstein-Barr virus infection. Sjögren, McArdle, Addison, Cushing, and paraneoplastic syndromes will also be exclusion criteria.

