### Randomization, blinding, and experimental groups

The EXTRAPHOTO trialists will enroll patients immediately after diagnosis of the two comorbidities and referral from recruitment centers. Patient enrollment and randomization, as well as data management, will be carried out by the Program in Biophotonics Applied to Health Sciences of the Nove de Julho University. The blinding will be applied to patients receiving phototherapy and a researcher reported to guide the exercise training. Thus, a researcher will be responsible for programming the phototherapy device, which can be turned on (phototherapy) or off (placebo) prior to application based on the randomization. A second researcher will guide the exercise training and will be blinded for phototherapy and/or placebo procedures. A third investigator will be blinded to allocation and will independently assess the outcomes. The statistical analysis will be performed by a fourth researcher, who will also be blinded to allocation of the patients.

The eligible participants will be instructed not to change their lifestyle or pharmacologic therapy during the study and will be randomized to one of the following groups:Control (CON): patients not subjected to any intervention; the phototherapy device will be turned off (placebo) as a blinded procedure for these participantsPhototherapy (PHO): patients subjected to phototherapyExercise training (EXT): patients subjected to aerobic exercise; the phototherapy device will be turned off (placebo) as a blinded procedure for these participantsPhototherapy plus exercise training (PHO + EXT): patients subjected to phototherapy and aerobic exercise training

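### The salivary serotonin comparison should adjust for baseline serotonin and baseline use of serotonin-acting drugs: the test is valid without this, but imprecise, and a null result is hard to read

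*Protocol article*

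**What the plan says.** The Abstract gives the aim: "A further aim is to determine whether the interventions can improve quality of life and modulate endogenous serotonin". The Statistical analysis section ranks the endpoint: "Quality of life as assessed by SF-36, salivary serotonin level, and overall parameters of pain will be secondary endpoints". The Salivary serotonin section defines the measure as a change: "mean serotonin changes from randomization to the end of withdrawal will be evaluated".

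Four places bear on background drugs:

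- Recruitment and inclusion criteria requires "optimized drug treatment, cognitive independence to respond to inquiries", without saying which drugs count.
- The same section excludes women for "presence of psychiatric disorders, missing teeth, and/or use of dentures" and for many diseases, but not for use of any drug class.
- Randomization, blinding, and experimental groups says that participants will be "instructed not to change their lifestyle or pharmacologic therapy during the study".
- The Background's general list of drugs for fibromyalgia names tricyclics and ends with "selective serotonin reuptake antagonists, nonsteroidal anti-inflammatory drugs, and opioids".

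The Statistical analysis section names two-way repeated-measures ANOVA with Bonferroni correction, or Kruskal-Wallis with Dunn's test. A Shapiro-Wilk test decides between them. No covariate is named for either route.

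**The concern.** The entry rule makes it likely, though not certain, that the sample mixes women on serotonin-acting drugs with women who take none. The serotonin endpoint is then averaged over both. Stable therapy and change from baseline remove a constant drug-related shift in level. They do not remove extra variation in change between users and non-users, or a different response to the interventions in users.

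With 15-20 women per arm, the stakes are precision and the reading of a null result. If users respond less, an effect in non-users is diluted in the pooled mean, and a non-significant result cannot tell no modulation from diluted modulation. The planned model uses neither the baseline serotonin value nor drug status as a covariate, although both could sharpen the comparison.

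**Working it through.** **Arm size.** The article's formula gives (1.96 × √(0.8 × 0.2) / 0.1)² = 61.5, close to the stated 60. It estimates a prevalence and contains no serotonin effect, SD or power. The article states 60 women, 20 per group and four groups, but 60/4 = 15 and 4 × 20 = 80. Both 15 and 20 per arm are therefore carried below.

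**Assumptions.** The article gives no share of users, no response in users and no serotonin SD. The user share p is taken as 0.3 to 0.5.

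**1. Chance imbalance.** With independent binomial counts X₁ and X₂ of users in two given arms of size n, P(|X₁ − X₂|/n ≥ 0.20) is:

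| n per arm | p = 0.3 | p = 0.5 |
|---|---|---|
| 15 | 0.318 | 0.362 |
| 20 | 0.226 | 0.268 |

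**2. Validity of the unadjusted test.** With two time points, the group-by-time test in a repeated-measures ANOVA is the one-way ANOVA of change scores. It was simulated 10,000 times per setting, with four arms, half the women users and no treatment effect. Settings were users changing by 0, 0.5 or 1 SD more than non-users, or having twice the SD of change. Type I error at nominal 5% was 4.6-5.0% with 15 per arm and 4.4-5.0% with 20. Imbalance in users does not inflate false positives.

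**3. Dilution.** Let r be the effect in users as a fraction of that in non-users. Then observed effect / effect in non-users = 1 − p(1 − r).

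- r = 0: 1 − 0.3 = 0.70 and 1 − 0.5 = 0.50.
- r = 0.5: 0.85 and 0.75.
- r = 1: 1.00 for any p.

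For r between 0 and 1 the range is 50-100%.

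**4. What the worst case would do to power.** The setting is a 1 SD effect in non-users, none in users (r = 0), two arms and two-sided 0.05.

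| n per arm | no users | p = 0.3 | p = 0.5 |
|---|---|---|---|
| 15 | 75% | 42% | 24% |
| 20 | 87% | 54% | 30-31% |

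Noise alone can also cost power. Suppose half are users, their changes have twice the SD, and the true difference is 1 SD of the non-users' change. The pooled SD is then √(0.5 × 1 + 0.5 × 4) = 1.58. By a normal approximation, power falls from 78% to 41% with 15 per arm and from 88% to 52% with 20.

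**5. Gain from adjustment.** Let ρ be the correlation of baseline and final serotonin, with equal variances. The standard error of an ANCOVA effect relative to that of a change-score effect is √((1 − ρ²) / (2(1 − ρ))) = √((1 + ρ)/2). For ρ = 0.3, 0.5 and 0.7 this is 0.806, 0.866 and 0.922, a cut of 19%, 13% and 8% from baseline serotonin alone. Adding baseline drug use moves the result either way: it removes variance if users differ, and costs a degree of freedom if they do not. Simulation with both covariates and 15 per arm gave cuts of about 7-24% over these correlations. ρ is an assumption.

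**6. Size of the non-user subgroup.** n(1 − p) is 10.5 and 7.5 women per arm at n = 15, and 14 and 10 at n = 20.

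**The case against.** The strongest reply is that the design already deals with the main threat. Allocation is random with a concurrent control arm, therapy is held constant, and the endpoint is a within-patient change. The planned comparison therefore estimates the average effect in women on stable usual treatment, which is a legitimate target. This stands, and it rules out three stronger readings that a reader might infer.

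- **A positive result could merely reflect unequal drug use.** Chance imbalance is already covered by the type I error rate, which stays near 5%.
- **The serotonin aim is not interpretable.** The comparison is valid. What suffers is precision and the meaning of a null.
- **The trial requires serotonin-acting drugs.** The Background list covers fibromyalgia treatment in general and also names gabapentinoids and opioids. It does not define the optimised treatment in the inclusion criteria, and the psychiatric exclusion may lower the number of users.

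It is also fair that no passage says users respond less. A flat 50-70% dilution would assume zero response in users, so the supportable range runs up to 100%.

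Finally, covariates for a secondary biomarker are often left to a fuller protocol or analysis plan, which is not shown. A missing covariate is therefore no error in itself. What remains is that the article does fix a test family, and its Kruskal-Wallis route cannot take a covariate. A better method for this endpoint is available at little cost.

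**Conclusion.** The point holds as a cheap improvement to a secondary endpoint. The unadjusted comparison of serotonin change is valid but less precise than it need be, and a null result would be ambiguous if users of serotonin-acting drugs respond less.

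On an assumed 30-50% users, a gap of at least 20 percentage points between two given arms has probability 32-36% at 15 per arm and 23-27% at 20. The pooled effect is 50-100% of the non-user effect for an unknown user response between none and full. Adjustment would cut the standard error by about 7-24% at 15 per arm, for assumed baseline-to-final correlations of 0.3-0.7. None of these inputs is in the article, so the sizes are illustrative. The direction of the gain from adjusting for baseline serotonin does not depend on the user share. Whether such drugs should be allowed is a clinical matter and is not judged here.

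**What to change.** 1. Code use of serotonin-acting drugs (yes/no) for each woman at baseline. The drug history needed to confirm optimised treatment should already supply it.
2. Compare final serotonin between arms by ANCOVA, with baseline serotonin and baseline drug use as covariates. If the values are non-normal, transform or rank them within this model in place of the Kruskal-Wallis route.
3. Report arm effects in users and non-users as a supportive, exploratory analysis only. With about 7-10 non-users per arm at 15 per arm, that estimate is too imprecise to be the main one.
4. Describe drug changes during the 10 weeks by arm, but do not adjust for them. They arise after randomisation, so adjusting could introduce bias.

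The cost is one coded variable and one or two degrees of freedom. Treatment and eligibility do not change. The Trial status section says that allocation is under way, so the coding should be settled now.
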